## Abstract

**Background:**

Cancer-related pain continues to be a major healthcare issue worldwide. Despite the availability of effective analgesic drugs, published guidelines and educational programs for Health Care Professionals (HCPs) the symptom is still under-diagnosed and its treatment is not appropriate in many patients. The objective of the study is to evaluate the efficacy of the Pac-IFicO programme in improving the quality of pain management in hospitalised cancer patients.

**Methods/design:**

This is a before-after cluster phase II study. After the before assessment, the experimental intervention – the Pac-IFicO programme – will be implemented in ten medicine, oncology and respiratory disease hospital wards. The same assessment will be repeated after the completion of the intervention. The Pac-IFicO programme is a complex intervention with multiple components. It includes focus group with ward professionals for identifying possible local obstacles to optimal pain control, informative material for the patients, an educational program performed through guides from the wards, and an organisational intervention to the ward. The primary end-point of the study is the proportion of cancer patients with severe pain. Secondary end-points include opioids administered in the wards, knowledge in pain management, and quality of pain management. We plan to recruit about 500 cancer patients. This sample size should be sufficient, after appropriate statistical adjustments for clustering, to detect an absolute decrease in the primary end-point from 20% to 9%.

**Discussion:**

This trial is aimed at exploring with an experimental approach the efficacy of a new quality improvement educational intervention.

**Trial registration:**

ClinicalTrials.gov: NCT02035098

## Background

Pain is one of the most common reasons for requesting health care service attention. The World Health Organization (WHO) estimates that 20% of individuals worldwide have some degree of chronic pain [1,2].

Despite the availability of effective analgesic drugs and of published guidelines [3-8] as well as of educational programs on the assessment and treatment of cancer-related pain [9], chronic pain is still under-diagnosed and its treatment is not adequate in many patients with both solid and haematological malignancies, in any stage of the disease [10,11].

Data from a systematic revision of the literature show that pain prevalence in cancer patients ranges from 33% in patients after curative treatment to 59% in patients on anticancer treatment, up to 64% in patients with advanced or terminal phase of disease [12].

Pain was undertreated in about 50% of the cancer patients evaluated in 26 trial by means of the Pain Management Index (PMI) [13] which evaluates the congruence between the patient’s reported level of pain and the intensity/strength of the analgesic therapy. Other surveys conducted in Italy and across Europe [10,14,15] confirmed these data, showing that pain was experienced in all cancer stages and that it was inadequately managed in a significant percentage of patients, both in early and metastatic stages, ranging between 56% and 82% and it is undertreated in oncology clinics, pain and palliative care and hospice canters [16-18].

Since 2010 pain assessment has been required by law for all patients in all Italian hospitals [19]. Major causes of undertreated pain in our country include: administration of analgesic drugs on request versus around the clock, prolonged use of no steroidal anti-inflammatory drugs [20], the employment of weak opioids, also for long periods of time, instead of strong opioids, the use of low doses of strong opioids [10,15] as well as the use of strong opioids only in metastatic and advanced disease stages, in order to avoid physical or psychological dependence, tolerance or side effects. All these factors were found to be related to malpractice among Health Care Professionals (HCPs).

The systematic management of cancer related pain is not included in the standard educational programs for clinicians in the Italian schools of medicine, whereas specific courses are available for nurses, who may also access a larger number of training courses on pain assessment and management, compared to clinicians [21-25]. On the whole, educational programs for health workers rarely meet the need for an adequate pain control in the daily practice. This may depend on different factors, such as : lack of comprehensive training programs for all the different health professionals involved in pain assessment and management, pain assessment carried out by nurses that is rarely followed by an effective evaluation and prescription by physicians, which demotivates nurses [9].

As indicated in the international guidelines, the optimal treatment of pain in cancer patients has recently been acknowledged as a major goal to guarantee the quality of care in hospitalized patients.

The availability of an effective protocol to improve the quality of pain control in hospitalized patients is mandatory in the daily practice in hospital units.

There is enough evidence supporting the potential effectiveness of the single issues (concerning the extent of information to the patients, education of HCPs and organizational support) of a program for the improvement of the quality of pain control in hospitalized patients [26-40]. The implementation and the effectiveness assessment of new pain educational programs is a mandatory issue (including education, information and organizational support) with the aim to improve pain measurement and control in all stages of oncological diseases. Such programs should have a multidisciplinary approach, thus involving nurses, physicians, psychologists, spiritual assistants and social workers, providing all health professionals with the needed information and training through a team work combining professional expertise and cure tailoring, and involving patients, who must be informed about pain and pain management and be encouraged to take an active role in their pain management [5,41].

A group of health professionals from different institutions developed a complex educational intervention aimed at improving pain control in hospitalized cancer patients. The acronym of the programme is Pac-IficO (P for Protocol, I for Information; F for Education and O for Organization). The Pac-IficO Programme includes a number of integrated interventions and is targeted to hospital wards, with the aim to significantly improve pain control in cancer patients.

The general aim of this study is assessing the effectiveness of the Pac-IFicO Programme in improving the quality of pain management in hospitalised cancer patients.

In this manuscript we report in detail the protocol used.

## Methods/design

### Objectives

#### *Primary aim*

The primary aim of this trial is to evaluate the effectiveness of the Pac-IFicO programme in improving the control of severe pain in cancer patients admitted to general medicine, oncology and respiratory disease wards of three Italian regions.

#### *Secondary aims*

The secondary aims of this study include the assessment of:

○ type and quantity of opioids administered in the wards;

○ knowledge of the ward professionals in pain management;

○ quality of pain management in cancer patients.

### Study design

This is a multicentre uncontrolled before–after cluster trial performed within hospital wards participating in the assessment of the Pac-IFicO programme.

The main objective of the Pac-IFicO programme is improving the quality of pain management in hospitalised cancer patients. The targets of the intervention are the professionals working in the hospital ward, but the outcomes of interest are assessed in clusters of patients from the hospital wards before and after the implementation of the Pac-IFicO programme.

The study is organised in different phases:

Preliminary phase

○ Identification of the eligible wards

“Before” assessment in the selected wards

○ Before evaluation according to the procedures of assessment

Implementation of the experimental intervention in the selected wards

○ Implementation of the PAC-IFicO programme

“After” assessment in the selected wards

○ After evaluation according to the procedures of assessment

### Procedures of the study

#### *Identification of the wards*

The three regional coordinators of the study obtained from local health authorities the list of all hospitals and wards of the region. For each ward the following information was collected: denomination and classification, number of beds, number of ordinary admissions per year with a primary or secondary diagnosis of tumour (ICD-IX 140-239) and their average length of stay in ward. An approximation of the punctual prevalence of the oncological patients was estimated for each ward from the last two information.

The process of identification of the eligible wards participating to this study is performed according to the following procedures:

➣ identification of all potential eligible units from the list of the hospital wards of each region (criteria 2-6 of the ward-level inclusion criteria);

➣ phone interview with the nurse coordinators on previous training on pain management received by the wards (criteria 1 of the ward-level exclusion criteria);

➣ random sampling, for each region, of the first eligible ward and subsequent evaluation of the consent from the Hospital management and the head of the ward to participate in the study. The procedure were repeated until two eligible units per region were identified.

The procedures and the dimensions of assessment for each identified ward include three levels:

Ward level

○ Information about the total consumption of opioids of the ward in the 6 months before and in the 6 months after the implementation of the Pac-IFicO programme were collected from the Hospital pharmacy.

Staff level

○ For all physicians and nurses of the ward information about qualification, years of service, training in pain management were collected.

○ Knowledge of the ward professionals in pain management were assessed before and after the implementation of the intervention by administering the Italian version of the Pain Attitudes and Knowledge Scale (PAK) [24,42];

Patient level

○ The quality of pain management is assessed before and after the implementation of the intervention by administering the APS-POK [43] to all eligible cancer patients in five weekly established sessions. The first session will be before T0) and thereafter one week apart: T7-T14-T21-T28. Each session will start at 14.00 on a midweek day. Eligible patients of each ward were identified by the nurse coordinator in the morning of the established day of assessment.

○ For all eligible cancer patient demographic and clinical information were collected. Moreover, date and time of evaluation, and causes for failed evaluation were also registered.

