### Sample size

To address the effectiveness of the Pac-Ifico Programme, a clustered sample size was estimated with an alpha error of 0.05 and a power of 80%, assuming an intraclass correlation coefficient (ICC) for the primary endpoint equal to 0.01. According to these assumptions we estimated that 10 hospital wards, with cluster size equal to 25 pre-intervention and 25 post-intervention patients corresponding to overall 500 patients, would be sufficient to detect an absolute decrease in the primary endpoint from 20% to 9%, corresponding to an odds ratio of 0.4.

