### Statistical analysis

Patients’ characteristics by pre and post-intervention groups and/or by centres were reported as means, frequency and percentage, for continuous and categorical variables, respectively. Student t-test for continuous variables and Pearson chi-square for categorical variables were used to compare pre-intervention vs. post-intervention group.

To account for the nested nature of the study design (i.e. patients clustered within wards), primary and secondary endpoints were analysed with a generalized hierarchical linear model [50,51].

Results comparing pre-intervention vs. post-intervention group were expressed in terms of mean differences and odds ratios (OR) along with their 95% confidence intervals (95% CI) for hierarchical linear and logistic models, respectively. Some analyses were adjusted for known confounders as reported in details in the specific tables.

Two-sided P-values < 0.05 were considered statistically significant. All the analyses were performed using the SAS Statistical Package Release 9.1 (SAS Institute, Cary, NC, USA).

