## Discussion

Although pain evaluation and management is codified both in available guidelines and, in Italy, also in the Law 38/2010, pain is still often uncontrolled both in cancer patients and in patients with non oncological chronic diseases.

Our Study aims to improve the quality of pain management in patients admitted to medicine, oncology and pneumology units in three Italian Regions: Liguria, Piemonte and Veneto.

By means of consolidated educational and organizational methodologies, the Pac-IFicO Programme actually reinforces current strategies for cancer related pain control according to international guidelines in some medicine, oncology and respiratory disease wards. Not only does the present study aim to consolidate scientific knowledge relating to clinical and non clinical recommendations contained in the object Program, but it also aims to assess the effectiveness of the whole Program as a tool to improve health care in cancer patients in pain.

The aim of this study was to assess whether the implementation of the programme may determine effective changes in the attitudes and behaviour of health professionals in view of a better practice, and whether these changes have a positive impact on the control of pain in cancer patients. The results will be analysed and interpreted at three levels: the ward level, the staff level, and the patient level, the last to evaluate the effectiveness of the induced changes in terms of an improved quality of health care.

One of the most innovative features of the present programme is the appointment of two Guides in the unit (a physician and a nurse, i.e. a small team) who will first attend a 4-day long training course, after which they will reproduce a “standard implementation” training to all their colleagues, including all the physicians and nurses within the involved unit. The hospital staff will thus become a source of continuous training, which multiplies by involving new professionals. Moreover, the monthly grand rounds on critical clinical cases, along with the peer to peer learning assessment interviews among the unit health professionals with the Guides strengthen and improve any educational initiative by including the whole involved staff.

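### The ward sampling rule yields 6 wards, but the abstract and the sample size section state 10; the article does not reconcile the two, and the 80% power belongs to 10

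*Protocol article*

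**What the plan says.** In the protocol article, Identification of the wards describes drawing eligible wards at random within each region and seeking consent. It then gives the stopping rule: "The procedure were repeated until two eligible units per region were identified". The number of regions is three throughout. The Primary aim refers to patients "admitted to general medicine, oncology and respiratory disease wards of three Italian regions", the Discussion places the study "in three Italian Regions: Liguria, Piemonte and Veneto", and the sampling section itself mentions three regional coordinators.

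Two other places give a different number of wards. The abstract (Methods/design) says that the programme "will be implemented in ten medicine, oncology and respiratory disease hospital wards". The Sample size section bases its calculation on "10 hospital wards, with cluster size equal to 25 pre-intervention and 25 post-intervention patients corresponding to overall 500 patients", with alpha 0.05, power 80%, an ICC of 0.01 and a fall in severe pain from 20% to 9%. The Statistical analysis section fixes the sidedness: "Two-sided P-values < 0.05 were considered statistically significant".

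**The concern.** Two wards in each of three regions is six, not ten. The article gives no larger quota for some regions, no second sampling round and no wards added outside the random draw. Ten is not divisible by three, so replacing the word two with any other single number would not repair the sentence.

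The number of wards sets the total number of patients, the degrees of freedom between wards and the power for the primary end-point. If six wards were sampled at the planned cluster size, the study would have 300 patients and clearly less than 80% power. If ten were used, the sampling description does not say how four of them were selected. In an uncontrolled before–after study, that matters for judging to which wards the result applies.

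**Working it through.** **Inputs (protocol article).** Rates 20% before and 9% after; alpha 0.05; ICC 0.01; 25 patients per ward per phase; 10 wards (all from Sample size). Two-sided test (Statistical analysis). Two wards per region (Identification of the wards). Three regions (Primary aim, Discussion). No dropout allowance is stated and none is used.

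**Ward count.** 2 × 3 = 6 wards; 6 × (25 + 25) = 300 patients. Sample size: 10 × (25 + 25) = 500 patients.

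**Reproducing the stated figure.** The pooled two-proportion formula for 80% power is

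n = [1.96·√(2·0.145·0.855) + 0.842·√(0.20·0.80 + 0.09·0.91)]² / 0.11² ≈ 160 per phase before clustering.

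The design effect is 1 + (m − 1)·0.01.

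- Counting all 50 patients of a ward as the cluster (m = 50): 1 + 49·0.01 = 1.49. Then 160 × 1.49 = 238.4 per phase, and 238.4/25 = 9.5, which rounds up to 10 wards.
- Counting 25 (m = 25): 1 + 24·0.01 = 1.24. Then 160 × 1.24 = 198.4 per phase, and 198.4/25 = 7.9, so 8 wards would do with a normal reference.

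The article does not say which method it used. Three variants come close to 80% at ten wards: the pooled test and the log odds ratio test, both at 1.49, and a t reference with (wards − 1) df at 1.24.

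**Power at 25 per ward per phase.** The effective number per phase is 25 × wards / design effect.

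| Method | 10 wards | 6 wards |
|---|---|---|
| Pooled test, design effect 1.49 | 81.9% | 60.2% |
| Log odds ratio test, design effect 1.49 | 79.8% | 58.1% |
| t reference (9 or 5 df), design effect 1.24 | 80.6% | 51.0% |
| Pooled test, design effect 1.24 | 88.3% | 68.3% |
| t reference (9 or 5 df), design effect 1.49 | 73.2% | 44.3% |
| Pooled test, ward effect cancels fully (factor 1 − 0.01 = 0.99) | 94.2% | 77.9% |

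The first three rows reproduce the stated 80% at ten wards, and give 51–60% at six. The last three do not reproduce it; they supply the outer limits of 44% and 78%.

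**More patients per ward.** 500 patients from 6 wards means 500/12 = 41.7 per ward per phase. The design effect is then 1 + 40.7·0.01 = 1.407 (m = 41.7) or 1 + 82.3·0.01 = 1.823 (m = 83.3). Power is 84% or 74% with the pooled test, and 67% or 56% with a t reference on 5 df.

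**The case against.** The strongest reply is that ten wards is probably what was meant. The abstract and the Sample size section agree, 10 × 50 = 500 is coherent, and the power can be reproduced. The sampling sentence is the only outlier, and if it is the error no power is lost. That stands, and it is why the power loss can only be stated conditionally. It does not remove the contradiction, because a reader following the sampling procedure still arrives at six wards.

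Second, 25 per ward per phase is a planning figure and not a cap. The protocol assesses all eligible patients in five weekly sessions. Six wards might yield more than 300 patients, and the article does not let one settle how many. This also stands. At 500 patients the shortfall shrinks or disappears, depending on the method.

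Third, the same wards are measured before and after, so a stable ward effect may partly or wholly cancel in the comparison. That is a fair point and raises the upper limit at six wards to about 78% with a normal reference.

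A reader might infer more: that the trial as designed has only about 50–68% power and cannot reach 500 patients, so that a negative result would tell us nothing. The article does not support this. It nowhere shows that six wards were used or that recruitment stops at 25. The 68% comes from a method that gives 88% at ten wards, so it does not match the stated 80%, and 50–68% does not bound the plausible values. The analysis also reports odds ratios with 95% confidence intervals; fewer wards would widen these but not make them worthless.

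**Conclusion.** The contradiction holds: six wards by the sampling rule, ten by the abstract and the Sample size section, with nothing to connect them. The stated power calculation is not itself wrong, since it is reproduced at ten wards.

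The effect on power is conditional. It arises only if the two-per-region rule was the one applied, and its size assumes 20% versus 9%, an ICC of 0.01 and the planned 25 patients per ward per phase. On those terms power drops from the stated 80% to about 51–60%, within wider limits of about 44–78%. Every method tried leaves it below 80% at that cluster size. If ten wards is the true plan, the loss is nil and the fault lies in how ward selection is described.

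**What to change.** Decide which number of wards is the plan and make Identification of the wards, the abstract and Sample size agree.

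- **If ten:** rewrite the stopping rule with regional quotas that add to ten (these must be unequal across three regions) and say how all ten wards are chosen. The power statement stays. The cost is one or two sentences.
- **If six:** state six wards in the abstract and in Sample size, give the matching number of patients, and restate the power with its method. At 25 per ward per phase that is 300 patients and about 51–60%. If 500 patients are still intended, state the roughly 42 per ward per phase that this requires and the power that follows: about 74–84% with a normal reference or 56–67% on 5 df, at the inflating design effects. The cost is again wording, but the stated power becomes less favourable at 300 patients and, by most of these methods, at 500.

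In either case, name the design effect and the reference distribution behind the power figure, so that it can be checked against the final number of wards.

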### End-points

#### *Primary end-point*

The primary end-point of the study is the percentage of hospitalized cancer patients with average severe pain (score 7-10) within the latest 24 hours in the after sample as compared to the before sample.

#### *Secondary end-points*

Ward level

○ Indicators about opioids administration includes: type and total amount of opioids administered in the wards to all patients;

Staff level

○ Knowledge and attitudes of the ward professionals in pain management were assessed with the Italian version of the Pain Attitudes and Knowledge Scale (PAK). The questionnaire was developed and validated by Lebovitz et al [44], and subsequently translated, adapted and validated into Italian [24,42]. The Italian version of the PAK includes 10 items, aiming to evaluate health professionals relating to their knowledge in the field of pain assessment, use of analgesics and pain management in oncological patients.

Patient level

○ The quality of pain management was assessed with the APS-POK. The questionnaire was originally developed and validated with the aim of assessing pain and pain control as perceived and rated by the patient [45]. The APS-POK is constituted of three major sections assessing: pain intensity and interference during the last 24 hours (9 items from the Pain Inventory), [46] patient’s satisfaction about pain treatment (3 items), possible prejudices preventing optimal pain management (7 items). The APS-POQ was translated and validated into Italian [43].

